### 13.3 Methods for Randomization and Stratification

Treatment assignments will be randomly generated using a computer program. Separate assignment lists will be generated for each stratum. Stratification factors are gender, Study Center, anticipated follow-up interval (3 or 5 years) and whether the patient is participating in both the vitamin D and calcium components or only the vitamin D component (the latter component is only for women who wish to take calcium supplements). Treatment assignments will be made in blocks to ensure equal numbers of patients across the treatment groups at various time intervals. The size of the blocks will vary in a random fashion. Randomization will occur only once a patient satisfies all eligibility criteria, including a successful run-in period.

### 13.4 Outcome Measures

For each subject, we will tabulate the number of mucosal lesions found, and record their size, histological characteristics, and location in the bowel. Each polyp will be classified (using standard criteria) as neoplastic (tubular, tubulovillous, villous, or serrated adenomas or cancer), hyperplastic, hamartomatous, retention, lymphoid, or other. In addition, for the neoplastic polyps, a statement with regard to the degree of atypia present will be made using standard criteria.

The main end point of the trial is the occurrence of neoplastic polyps of the large bowel in the interval between randomization and the anticipated follow-up colonoscopy (3 or 5 years after the qualifying exam). As in our previous trials, our primary endpoint will be a dichotomous measure of any occurrence of neoplastic polyps (adenomas). Secondary analyses will focus on the number and size of neoplastic polyps, the occurrence of advanced adenomas, and effects within subgroups defined by baseline 25-OH vitamin D levels and by VDR genotype.

### 13.5 Statistical Analysis

All analyses will be conducted according to the principle of intention to treat. The analysis population will consist of all randomized patients, with patients being grouped according to randomized treatment assignment regardless of whether this treatment was actually delivered.

To address our primary hypotheses, the primary statistical analysis will use contingency tables and standard 2 tests to compare adenoma occurrence between treatment groups. There will be three primary comparisons: 1) vitamin D versus no vitamin D, and 2) calcium versus no calcium and 3) vitamin D + calcium versus calcium alone. Comparison 1 will collapse numbers of subjects across calcium supplementation groups to assess the marginal effect of vitamin D. Comparison 2 will collapse numbers of subjects across the vitamin D supplementation groups to assess the marginal calcium effect and will exclude women who do not consent to randomization in the calcium component of the study. Comparison 3 will focus only on subjects taking calcium; no collapsing is necessary. Effects will be summarized using risk ratios rather than odds ratios to improve interpretation. Two-sided significance levels of 0.05 will be taken to denote statistical significance.

As in our previous trials, subsequent, more detailed, multivariate analyses will consist of generalized linear models for binary data to estimate adjusted risk ratios (i.e., using a log link function) and confidence intervals for neoplastic polyp occurrence among the treatment groups. We anticipate that the distribution of relevant covariables will be approximately balanced across the treatment groups because of random assignment in a relatively large sample. Some imbalances may occur, making it necessary to critically examine possible covariates. These include number of previous adenomas, size of qualifying adenomas, selected dietary variables (e.g., calcium intake) or sunlight exposure. The distribution by treatment group of these covariates (for the whole sample as well as by center) will be assessed. For those variables with large and systematic imbalances, stratified analyses will be employed to confirm or modify the preliminary analyses. Factors used to stratify the randomization (center, planned follow-up interval, full factorial participation) will be included as covariates. We will also use these models to evaluate the interaction between vitamin D supplementation and calcium supplementation. The interaction effect will be tested by including the appropriate product term in the model. This interaction analysis will include only those subjects enrolled in the full factorial design (i.e., women wishing to take calcium supplements will be excluded). We do not expect differential treatment effects according to age, gender or race, but we will consider the corresponding interactions for the treatments.

Analyses pertaining to the secondary hypotheses will use methods similar to those described for the primary hypotheses. The comparison of calcium + vitamin D versus vitamin D alone (hypotheses 4) will be dealt with in the same manner as the primary hypotheses. Comparison of treatment effects within subgroups defined by VDR genotype or baseline vitamin D level will initially involve contingency tables stratified by genotype or vitamin D level. We will then apply generalized linear models with appropriate interaction terms and other covariates. If a possible (i.e., p < 0.10) interaction is observed, we will focus on effects within strata of the effect-modifying factor. In some analyses we expect to be able to consider the genotype data as a 3-level variable (homozygous wild type, heterozygous, homozygous variant) since the prevalence of the least common of these (homozygote variant) is approximately 15% for both the polymorphisms used. Some analyses, however, will require grouping the heterozygous subjects with those who are homozygous variant.

In addition to the planned treatment comparisons, we will conduct important subgroup analyses. For example, we will assess the treatment effects according to self-reported NSAID use during the trial. We will group subjects as having low, medium and high NSAID use during the study and add this exposure to our regression models and assess its main effect and its modification of the vitamin D and calcium risk ratios. In similar analyses, we will assess the impact of baseline vitamin D levels and VDR polymorphisms as main effects and as modifiers of the intervention effects.

We will also conduct analyses regarding the number and characteristics of polyps. The number of adenomas per patient will be evaluated using contingency tables (with groupings such as 0, 1, 2+ adenomas) as well as multivariate Poisson regression with the counts themselves as the dependent variable. The size of neoplastic polyps will be incorporated using various dichotomous endpoints; if sufficient adenomas at least a cm in diameter are found, we will use that cut point. Adenomas with various histological characteristics (serrated, tubulovillous/villous, advanced dysplasia/cancer) will also be considered as dichotomous endpoints as outlined above for all adenomas; in particular, we will assess effects on “advanced histology adenomas” (villous component, advanced dysplasia) or “advanced adenomas (advanced histology or 1+ cm. in diameter).

Analyses regarding the main hypotheses will not be possible until all subjects have completed follow-up, after the period covered by this application. We do not anticipate stopping this trial early for efficacy, since early termination biases estimates of effect,[189](#_ENREF_189) and in this population under colonoscopic surveillance, there is little likelihood of harm from continuing until the planned study completion. However, for toxicity, we anticipate discussing with the Safety and Data Monitoring Committee the adoption of stopping guidelines that account for multiple analyses over time (e.g., using O’Brien-Fleming boundaries).[190](#_ENREF_190) Such guidelines have been established in our Aspirin/Folate Polyp Prevention Study to consider possible treatment effects on mortality and coronary heart disease.

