***3.0 Summary of Study Plan***

*3.1 Overview*

This study is a double-blind, placebo-controlled trial of vitamin D and/or calcium supplementation for the prevention of large bowel adenomas. Subjects will be recruited from 11 Study Centers in North America. Eligible subjects will have had at least one large bowel adenoma removed in the 4 months prior to study entry and no remaining polyps in the bowel after complete colonoscopic examination. Participants will be randomized in a modified 2 x 2 factorial design to vitamin D (1000 IU/day), calcium carbonate (1200 mg elemental calcium/day), both agents, or placebo only. Women who decline to forego calcium supplementation will be randomized only to calcium alone or to calcium plus vitamin D. Randomization will be stratified by gender, Study Center of recruitment, and anticipated follow-up interval (see below), and will be conducted separately for female subjects randomized only to vitamin D. Participants will agree to avoid taking study agents outside the trial and will initially be observed in a 3-month placebo run-in period to identify (and exclude before randomization) subjects likely not to adhere to the study regimen. We anticipate enrolling about 3000 participants to reach a total of approximately 2400 randomized subjects. As safety measures, blood levels of calcium, creatinine and 25-(OH)-vitamin D will be obtained at baseline and 1 year after randomization, as well as 3 years after randomization for subjects with a 5-year surveillance cycle. Every six months after randomization subjects will complete a questionnaire regarding compliance with study agents, use of medications and vitamin/mineral supplements, illnesses, hospitalizations, and dietary intake of calcium and vitamin D.

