***5.0 Agent Information and Administration***

- 1. *Name of agents and study arms*

There will be four arms in the study:

1. placebo
2. calcium carbonate (3 gm/daily; 1200 mg elemental calcium/daily)
3. vitamin D3 (1000 IU/daily)
4. calcium carbonate and vitamin D3

*5.2 Assignment and Duration of Study Treatment*

Men will be randomly assigned to each of the treatment groups at equal frequency. Due to recommendations for high calcium intake among post-menopausal women and the common use of calcium supplements in that population group, women will have the option of being randomized to calcium or to calcium plus vitamin D (arm 2 or 4). In this way, they will receive 3 gm of supplemental calcium carbonate daily as part of the study. Based on our experience in the Aspirin-Folate Polyp Prevention Study, we assume that 35% of women will accept the full factorial randomization and 65% will wish to continue calcium supplementation and accept the restricted randomization (two arm). There will be separate randomization procedures for subjects being randomized to both agents and for women taking calcium who will be randomized only to vitamin D. Although it will not be encouraged, at any time after enrollment, women who are in the Full Factorial component of the study will have the option to change their mind and switch to the 2 Arm component of the study. Study tablets shipped to these subjects will be changed accordingly. For statistical analyses purposes they will be analyzed as per the original treatment group that they were randomized to. All randomization will be stratified by Study Center of recruitment and scheduled colonoscopic follow-up (3 years or 5 years).

The follow-up interval for colonoscopy recommended by a patient's endoscopist, either 3 or 5 years, will determine the duration of exposure to the study agents. For a 3 year follow-up interval, the duration of exposure to the study agents will be approximately two and one half years (30 months) due to the subtraction of the initial time required for subject identification and recruitment (up to four months) and a subsequent three month run-in period during which subjects take placebo pills (full factorial) or calcium alone (two arm). Likewise, the duration of exposure to the study agents will be approximately 4 and one half years (54 months) for a 5 year follow-up interval.

*5.3 Dose selection – safety and efficacy*

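### The primary chi-square ignores the strata used in randomization: valid but slightly conservative; the adjusted models omit gender, and imbalance-driven analyses may change the primary result

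*Protocol*

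**What the plan says.** **Randomization.** Section 13.3 generates a separate assignment list for each stratum: "Stratification factors are gender, Study Center, anticipated follow-up interval (3 or 5 years"). A fourth factor there separates full-factorial subjects from women randomized to vitamin D alone. Section 3.1 agrees on gender: "Randomization will be stratified by gender, Study Center of recruitment, and anticipated follow-up interval". Section 5.2 does not mention it: "All randomization will be stratified by Study Center of recruitment and scheduled colonoscopic follow-up (3 years or 5 years").

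**Primary analysis.** Section 13.5 states that "the primary statistical analysis will use contingency tables and standard" chi-square tests for vitamin D versus none, calcium versus none, and vitamin D plus calcium versus calcium. The collapsing described there is across the arms of the other supplement. No stratification by randomization factors is mentioned. The decision rule is "Two-sided significance levels of 0.05 will be taken to denote statistical significance". The footnote to Table 1 in section 13.2 bases power on the same chi-square test.

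**Later analyses.** Section 13.5 then describes more detailed log-link models giving adjusted risk ratios: "Factors used to stratify the randomization (center, planned follow-up interval, full factorial participation) will be included as covariates". Gender appears in that section only as a possible treatment interaction. For other baseline variables the rule is: "For those variables with large and systematic imbalances, stratified analyses will be employed to confirm or modify the preliminary analyses".

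**The concern.** Stratified randomization balances the arms within each stratum and so removes between-stratum risk differences from the true variance of the treatment comparison. An analysis that ignores the strata still counts those differences as noise. Its standard error is then too large and its test rejects slightly too seldom under the null hypothesis.

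The protocol gives some reason to expect the strata to differ in risk. Section 4.1 says adenomas are somewhat more prevalent in men. Two-arm women all take calcium, so on the section 13.2 assumptions their expected rate without vitamin D is 0.37 × 0.80 = 29.6%, against (37% + 29.6%)/2 = 33.3% in the full factorial. Section 5.2 gives about 30 or 54 months of exposure depending on the interval. Nothing is said about risk by center.

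Two further points affect how the result will be read. The list of stratification factors for the adjusted models does not match the randomization. And an adjustment chosen after seeing imbalance, with no threshold and an open list of candidate variables, is allowed to change the primary finding.

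**Working it through.** **1. Reproduce Table 1, to confirm which test was powered.** Inputs from section 13.2: placebo rate p = 0.37, calcium RR 0.80, vitamin D RR 0.75, no interaction, two-sided 0.05, and 1103, 816 and 695 subjects per group.

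Control rates:
- Vitamin D: (408 × 0.37 + 695 × 0.37 × 0.80)/1103 = 0.323
- Calcium: (0.37 + 0.37 × 0.75)/2 = 0.324
- Vitamin D + calcium vs calcium: 0.37 × 0.80 = 0.296

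Power = Φ{(|p1 − p2| − 1.96·s0)/s1}, with s0 = √(2p̄(1 − p̄)/n) and s1 = √((p1(1 − p1) + p2(1 − p2))/n).

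Example, third comparison at RR 0.80: p1 = 0.296, p2 = 0.2368, s0 = 0.02371, s1 = 0.02366. Power = Φ{(0.0592 − 0.0465)/0.02366} = Φ(0.54) = 0.705; the plan states 0.70.

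| Comparison | Plan, RR 0.70 / 0.75 / 0.80 / 0.85 | Recomputed |
|---|---|---|
| Vitamin D | >0.99 / 0.99 / 0.92 / 0.70 | 0.999 / 0.988 / 0.917 / 0.701 |
| Calcium | >0.99 / 0.95 / 0.82 / 0.57 | 0.993 / 0.953 / 0.821 / 0.572 |
| Vitamin D + calcium vs calcium | 0.97 / 0.88 / 0.70 / 0.46 | 0.969 / 0.884 / 0.705 / 0.459 |

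All twelve entries reproduce. The stated power is that of the unstratified test.

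**2. Is the unstratified test valid?** Full-factorial subjects are allocated equally to four arms and two-arm women equally to two. Every primary comparison is therefore 1:1 within every stratum. No stratum is over-represented in either group, so there is no bias and no inflation of type I error.

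**3. How conservative is it?** Simulation, 20,000 trials per scenario, with 1:1 allocation within 11 centers × 2 intervals × (men, full-factorial women, two-arm women). The plain chi-square is compared with a Cochran-Mantel-Haenszel (CMH) test over all strata. The stratum effects are assumptions:
- none
- moderate: center SD 0.25 on the log-odds scale, odds ratio 1.3 each for interval and gender
- strong: center SD 0.5, odds ratios 1.6

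Control rates are 32%, 32% and 30%, as rounded in Table 1. Intervals are split equally and centers are of equal size, also by assumption.

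| Comparison | Scenario | Type I, chi-square | Type I, CMH | Power at RR 0.80, chi-square | Power, CMH |
|---|---|---|---|---|---|
| Vitamin D | none | 0.049 | 0.049 | 0.911 | 0.911 |
| Vitamin D | moderate | 0.050 | 0.052 | 0.910 | 0.913 |
| Vitamin D | strong | 0.039 | 0.048 | 0.919 | 0.927 |
| Calcium | none | 0.051 | 0.051 | 0.817 | 0.816 |
| Calcium | moderate | 0.048 | 0.050 | 0.816 | 0.820 |
| Calcium | strong | 0.044 | 0.050 | 0.821 | 0.829 |
| D + calcium vs calcium | none | 0.054 | 0.054 | 0.722 | 0.721 |
| D + calcium vs calcium | moderate | 0.045 | 0.047 | 0.723 | 0.727 |
| D + calcium vs calcium | strong | 0.038 | 0.049 | 0.725 | 0.744 |

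Monte Carlo standard error is √(0.05 × 0.95/20,000) = 0.0015 for type I error and √(0.72 × 0.28/20,000) = 0.003 for power near 0.72. Both tests were run on the same simulated trials. Center effects were redrawn for each run, so compare the two tests within a run, not one row with another.

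**4. Closed-form check.** The true variance is a fraction 1 − σ²/(p(1 − p)) of what the chi-square assumes, where σ is the SD of risk across strata. In the strong type I run for vitamin D, σ = 0.139 and p = 0.32: 1 − 0.0193/0.2176 = 0.911. The effective critical value is 1.96/√0.911 = 2.05, giving type I error 0.040 (simulated 0.039). For the third comparison, σ = 0.141 and p = 0.30 give 0.039 (simulated 0.038).

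**5. Effect of leaving out gender.** CMH without gender against CMH with gender, power in the strong scenario: 0.9264 vs 0.9271, 0.8273 vs 0.8287, and 0.7429 vs 0.7442. The difference is below 0.002. The participation covariate already separates 624 of the 960 women. It leaves 336 full-factorial women together with 1440 men, and in the calcium comparison it does not vary at all.

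**6. The imbalance rule.** Section 13.5 names the chi-square as primary. It then lets a later, data-triggered stratified analysis alter what that test found. It gives no threshold for large or systematic imbalance, and its candidate list is illustrative (adenoma number and size, selected dietary variables, sunlight).

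**The case against.** The strongest reply is that nothing here is an error of inference. The chi-square is unbiased and controls type I error. Table 1 is powered on that same test and reproduces. Section 13.5 names it as primary and places the adjusted models after it, with the stratification factors as covariates. The gain from stratifying is a point or two at most, and it rests on stratum effects that the protocol does not give. Choosing an adjusted over an unadjusted analysis, and fixing a covariate list, is often left to the analysis plan. Most of this stands, and it limits the size of the point.

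It does not dispose of it. The protocol itself fixes the primary test, lists the strata inconsistently, and states the rule that lets later analyses alter the result. These are not details left open for a separate plan.

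A reader might infer more than the documents support:
- **That the primary test is invalid or biased.** It is not; allocation is 1:1 within strata.
- **That the trial has no defined primary result.** Section 13.5 does name a primary test; the fault is the later licence to alter what it shows.
- **That covariates are to be added to the models after imbalance is seen.** For imbalanced variables the text prescribes stratified analyses. The choice is still data-driven, but it is a different procedure.
- **That omitting gender harms the adjusted results.** The numerical effect is negligible; the contradiction with section 13.3 is what needs correcting.

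**Conclusion.** The point holds as a modest improvement with two wording corrections. With moderate to strong assumed stratum effects, the unstratified chi-square has type I error of about 0.038 to 0.050, against 0.047 to 0.052 for the stratified test. It gives up about 0.3 to 0.4 points of power at RR 0.80 in the moderate scenario and 0.8 to 2.0 points in the strong one. The largest loss (0.725 against 0.744) falls on vitamin D plus calcium versus calcium, where the plan's own power is lowest (0.70). If the strata do not differ in risk, there is no loss.

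The gender omission and the differing lists in sections 3.1, 5.2 and 13.3 are inconsistencies of record with negligible numerical effect. The open-ended imbalance rule cannot be sized from the documents. It matters more for how the trial is read, because it lets an analysis chosen after seeing the data alter the primary finding.

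**What to change.** - **Section 13.5, primary analysis.** Name one stratified analysis for all three comparisons, for example a Mantel-Haenszel risk ratio with a CMH test over the randomization strata: gender, center, interval, and component where it varies. Keep the unadjusted chi-square as supportive. At most 11 × 2 × 3 = 66 strata arise for vitamin D and for vitamin D plus calcium versus calcium, and 11 × 2 × 2 = 44 for calcium. That averages about 33, 21 and 37 subjects per stratum (2206/66, 1390/66, 1632/44). Some cells will be small, which the CMH test tolerates.
- **Section 13.5, adjusted models.** Add gender to the stratification covariates.
- **Section 13.5, imbalance rule.** Delete the words *or modify*, and state that analyses prompted by observed imbalance are sensitivity analyses only.
- **Section 5.2.** Reconcile the stratification factors with sections 3.1 and 13.3.

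The cost is a few sentences and slightly more analysis work. The stratification variables are known at randomization, and no change in sample size is needed.

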### 13.6 Assumptions

Only standard assumptions for statistical analysis will be made. These include: (1) that the study sample is representative of the eligible patient population; (2) the protocol procedures for treatment and follow-up of individual patients will result in an unbiased estimate of the treatment effect; (3) regression models used for the multivariate analyses appropriately fit the empiric data. Because this study uses a “gold-standard” approach in its design, namely with random treatment assignment and double blinding of treatment assignment, the possibility of systematic bias is minimal.

### 13.7 Compliance and missing data

Missing data may arise due to patients missing follow-up colonoscopies. In past studies by the Polyp Prevention Group, the percent of missing exams has been small. In addition, because the treatment assignment is random, and both subjects and investigators are blinded to treatment assignments, it is not likely that missing exams will generate a bias. Patients with missing follow-up data will be excluded from the statistical analysis of the main endpoints.

